### 3.2. Study Setting

To have sufficient power, we recommend using real-world secondary data derived from electronic health records or administrative claims data that can be linked on an individual level to birth registries and outcomes in offspring (mother-child linkage). The specific study setting will be defined by the availability and nature of the data source(s) utilised and will depend on the country or region covered by the data source. To assess whether data sources are fit for purpose, we stress the importance of ascertainment the accuracy of estimating the start and end of pregnancy, the ability to detect ongoing pregnancies, the capacity to identify exposure to RSV vaccines including timing of vaccine dose, the feasibility of linking mother and child, the capability to measure outcomes and confounders of interest, and the lag time for data availability for each study component. We recommend the use of quality indicators and external benchmarks to assess whether a data source is fit for purpose [18,19]. Key aspects of this evaluation include:Population coverage: The data must cover a representative sample of the population under study. This includes demographics such as age, sex, ethnicity, and geographic location.Data granularity: The data must be granular enough to capture individual-level information on healthcare encounters, including diagnoses, procedures, prescriptions, and outcomes.Longitudinal data: Longitudinal data, tracking individuals over time, is essential for understanding disease progression, treatment patterns, and outcomes.Data quality: High-quality data is crucial for reliable analysis. This involves accurate information recording, standardised coding systems, and measures to address missing or erroneous data.Data linkage: The ability to link data across different sources (e.g., primary care, hospitals, pharmacies, birth registers) enables a comprehensive view of healthcare utilisation and outcomes.Privacy and ethical considerations: Data sources must adhere to strict privacy regulations and ethical guidelines to protect patient confidentiality and ensure informed consent.Timeliness: Timely updates ensure that researchers can access the most current information, allowing for real-time or near-real-time analyses.

### 3.3. Study Period

The first maternal vaccine was launched on 23 August 2023 [4]. In a hypothetical scenario focused on a study of its safety, we propose commencing data collection retrospectively from 24 August 2022. This means that gathering data starting from the day following approval, allowing for a one-year look-back period. This period is essential for capturing prior medical history, including diseases, comorbidities, and medication use, which are critical factors to consider in the study’s analysis and interpretation. Data collection would continue until the last data availability for each data access provider based on the calendar date of the last data extraction. Given the anticipated need for a significant number of participants, we expect a follow-up period of at least 5 years, with the latest data extraction planned for 2029. However, we recommend regular progress reports, with reporting triggered by the number of exposures.

### 3.4. Study Population

The study population comprises all pregnant women who receive an RSV vaccine during pregnancy from the earliest indicated timing of gestation for which the vaccine is licensed and a matched comparator group of pregnant women who did not receive the RSV vaccine or received another RSV vaccine. Identification of pregnancies may vary across data sources which is very important since most data sources that link to birth registries only detect pregnancies when they end. Validated data source-specific algorithms or the ConcePTION pregnancy algorithm could be employed to determine the start and end dates of ongoing pregnancies. The ConcePTION algorithm was created to identify ongoing pregnancies using diagnosis and procedure data related to pregnancy [20]. The identification of ongoing pregnancies is important to avoid selection bias towards pregnancies that end prematurely. In instances where pregnancy data are only available when the pregnancy has ended, a minimum of 10 months of administrative follow-up from the last menstrual period (LMP) in the data source, unless they died, is recommended for all pregnancy and birth outcomes. This period covers the gestational period plus an additional month to identify offspring outcomes at birth [17]. It is important to anticipate that women may have more than one pregnancy, and those subsequent pregnancies could be included to increase power.

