In the MATISSE trial, there was no evidence of a difference in the percentage of preterm births between the vaccine and placebo groups overall. However, analyses stratified by income level revealed a statistically significant difference in upper-middle-income countries [10]. Of note, another trial of a candidate maternal RSV vaccine of a similar type stopped early due to a higher risk of preterm birth in the vaccine group [11]. As the first vaccine to be approved for maternal indication and given this potential uncertainty about preterm birth, the regulatory agencies each approved the vaccine to be used at different gestational ages [12]. The EMA decided that the vaccine could be administered beginning at 24 weeks of gestation. The FDA approved vaccination of pregnant women at 32 through 36 weeks of gestation, while the MHRA has recommended that the vaccine may be given in the third trimester of pregnancy (weeks 28 to 36 of gestation) [13].

In light of the importance of addressing gaps in safety data, a protocol for a PASS to assess the safety of this RSV vaccine in pregnant women and their offspring in real-world settings was developed as an additional pharmacovigilance activity outlined in the EU and UK-approved risk management plans and as a post-marketing requirement to the FDA [14,15]. This manuscript provides a generic framework of the PASS protocol to assist researchers in the preparation of their own protocols during the post-marketing phase in the coming years.

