## 2. Objectives

The primary objective of a PASS on maternal RSV immunisation study is to estimate the occurrence of adverse maternal, pregnancy and birth outcomes in women who receive the vaccine during pregnancy (and their offspring), compared with a matched comparator group of pregnant women who do not receive the RSV vaccine during pregnancy (and their offspring). The secondary objectives may include assessing the occurrence of these adverse outcomes in immunocompromised or high-risk pregnant women who receive the RSV vaccine compared to those who do not, as these groups were not studied in clinical trials. Due to variations in timing of authorised administration, another objective may be to estimate the occurrence of adverse outcomes by gestational week of vaccination to better understand possible effect modification by week of gestation.

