## 3. Methods

### 3.1. Study Design

We recommend an observational retrospective comparative cohort study of pregnant women who receive the RSV vaccine compared to an unexposed pregnant comparator group (or an active comparator group when there is one). To assess whether the RSV vaccine increases the risk of any adverse outcome in pregnancy or offspring, we propose designing the study to emulate a hypothetical pragmatic randomised trial (Table 1) [16]. This trial would assess the safety of administering one dose of the RSV vaccine between 24 and 36 weeks of gestation in pregnant women compared to pregnant women who do not receive an RSV vaccine (Figure 1A). As we cannot truly randomise participants, we need to emulate this feature by carefully addressing confounding biases through various techniques such as matching and careful assessment of inclusion criteria. These techniques also have the potential to address both selection bias and immortal time bias. Time zero, designated as day 0, marks the point at which the eligibility criteria are fulfilled, and the RSV vaccine is administered to the pregnant woman.

At Time zero, exposed participants should be matched to unexposed pregnant participants eligible to receive the vaccine (1:N ratio) based on (Figure 1B):Gestational age (same week of gestation) to account for timing of vaccination in pregnancy and the risk of preterm birthCalendar time (same week) because of RSV seasonality and probability of exposureMaternal age (year of birth) because of the association with adverse pregnancy outcomesImmunocompromised status because of the association with adverse maternal outcomesHigh-risk pregnancy because of the association with adverse pregnancy outcomes

Additional characteristics may be added that would confound the association.

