In addition to outcome misclassification, it is also crucial to address exposure misclassification. Since RSV vaccination has only recently received approval for maternal immunisation, and many countries’ National Immunisation Technical Advisory Groups have yet to decide on its inclusion in routine immunisation schedules, it can be challenging to determine whether current data sources accurately capture RSV vaccination. This challenge is reflected by the current situation in Europe, where other maternal immunisation practices vary widely across countries, and some prefer to provide monoclonal antibodies or vaccines to neonates [2,48] Therefore, before commencing data collection, it is imperative to liaise with relevant public health organisations to understand if and how RSV vaccination will be integrated into routine immunisation programs for maternal immunisation and in which settings it is provided. Subsequently, it is essential to verify if the data source adequately captures this information and compare it with national statistics to ensure comprehensive coverage and prevent exposure misclassification in the comparator group.

It is important to note that a non-exposed comparator group may be chosen because presently there is only one approved maternal vaccine for preventing RSV infection in offspring. In the event that other RSV vaccines receive approval, it is crucial to consider their inclusion in the study design. This necessitates either incorporating all different RSV vaccines in the exposed group or excluding women specifically vaccinated with other RSV vaccines from the unexposed group.

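### Section 3.4 lets recipients of another RSV vaccine fit both the exposed and the comparator group and does not bar pooling them with unvaccinated women, at odds with the primary objective, Table 1 and the Discussion

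*Protocol article*

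**What the plan says.** Section 3.4 (Study Population) defines both groups in one sentence. The exposed group is "all pregnant women who receive an RSV vaccine during pregnancy from the earliest indicated timing of gestation" at which the product is licensed. The comparator is "a matched comparator group of pregnant women who did not receive the RSV vaccine or received another RSV vaccine".

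Other parts of the article describe the comparator differently:

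- **Section 2 (Objectives):** the primary objective compares vaccinated women with "a matched comparator group of pregnant women who do not receive the RSV vaccine during pregnancy".
- **Section 3.1 (Study Design):** the target trial sets one dose against receipt of no RSV vaccine. The same section allows, in parentheses, a substitute for the unexposed group: "or an active comparator group when there is one". Its follow-up paragraph and the follow-up row of Table 1 repeat that alternative.
- **Table 1, treatment strategies:** the emulation has two strategies, RSV vaccination and no RSV vaccination.
- **Section 3.6 (Exposure):** exposure is RSV vaccination in pregnancy, with no product named.
- **Section 3.9 (Study Size):** each vaccinated woman is compared with N unvaccinated women.
- **Section 4 (Discussion):** if further RSV vaccines are approved, the design calls for either "incorporating all different RSV vaccines in the exposed group or excluding women specifically vaccinated with other RSV vaccines from the unexposed group".

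**The concern.** Two things are unsettled in Section 3.4. First, the groups overlap: a recipient of a second product meets the definition of the exposed group and of the comparator. Second, the section does not say whether the two kinds of comparator are alternatives or may be combined. The exclusions in Section 3.5 do not settle it. They cover RSV vaccination before the current pregnancy or outside the licensed weeks, not a different product given in this pregnancy within its licensed weeks.

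The stake is the outcome the Discussion treats as primary, preterm birth. The Introduction reports that "another trial of a candidate maternal RSV vaccine of a similar type stopped early due to a higher risk of preterm birth", so a risk shared across similar products is the protocol's own worry. A comparator that contains recipients of such a product weakens that signal, and one made up entirely of them removes it. The article is a template for other teams' protocols, so an ambiguity here can be carried into several studies.

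**Working it through.** **1. Side-by-side reading.** Take a woman given a second RSV product at 30 weeks of the current pregnancy, with that week inside its licence.

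| Place | Where she belongs |
|---|---|
| 3.4, exposed clause | Exposed |
| 3.4, comparator clause | Comparator |
| 3.6 | Exposed |
| Table 1, treatment strategies | Exposed, not comparator |
| 2 and 3.1 (target trial) | Not in an unvaccinated comparator |
| 3.5 | Not excluded |
| 4 | Exposed, or excluded from the unexposed group |

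Section 3.4 lists not receiving the vaccine and receiving another one as two separate conditions. The phrase in the primary objective therefore matches only the first.

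**2. The protocol's own figure.** Section 3.9 states about 1200 pregnancies ending in live birth to detect a risk ratio (RR) of 1.5 for preterm birth, with alpha 5% and power 80%. Assumptions: two-sided test, comparator risk p0 = 6% (the top of the stated 0.2% to 6.0% range), N = 1. Then p1 = 0.06 × 1.5 = 0.09, the mean risk is 0.075, and

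n = [1.960 × √(2 × 0.075 × 0.925) + 0.842 × √(0.09 × 0.91 + 0.06 × 0.94)]² / 0.03² = 1209 exposed.

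This reproduces the stated figure. At 1:2 the result is 884 and at 1:4 it is 720, so 1200 corresponds to the exposed group at 1:1. It presumes that the whole comparator group is at the unvaccinated risk.

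**3. Scenario for a pooled comparator.** Let s be the share of comparators who received another RSV vaccine, and suppose that product has the same true RR of 1.5. Neither value is in the document.

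Comparator risk = 0.06 × (1 + 0.5s); expected RR = 1.5 / (1 + 0.5s).

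- s = 10%: 1.5 / 1.05 = 1.43
- s = 25%: 1.5 / 1.125 = 1.33
- s = 30%: 1.5 / 1.15 = 1.30
- s = 50%: 1.5 / 1.25 = 1.20
- s = 100% (active comparator only): 1.5 / 1.5 = 1.00

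These ratios do not depend on N. Power with 1200 exposed women, from the same two-proportion test:

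| s | Power at 1:1 | Power at 1:4 |
|---|---|---|
| 0 | 79.7% | 94.5% |
| 10% | 70% | 89% |
| 25% | 53% | 75% |
| 50% | 27% | 41.5% |

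If the second product carried no risk there would be no dilution. If it carried a higher risk than the study product, the RR against an active comparator could fall below 1.

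**The case against.** The best defence is that the clause in 3.4 names a choice of design, not a mixture. Section 3.1 and the follow-up row of Table 1 both present the active comparator as an alternative to the unexposed group, and no sentence describes a combined group. Matching in Section 3.1 is to unexposed women, and the study size is set against unvaccinated women. A head-to-head contrast is a legitimate design, and a generic protocol may leave it open. Only one maternal product is approved, so s is about zero today.

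Most of this stands. It limits what can be claimed, and four stronger inferences fail:

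- *That the protocol prescribes a mixed comparator.* It does not. Pooling is a reading that the text fails to exclude.
- *That the Discussion forbids an active comparator.* Its rule concerns keeping other-product recipients out of the unexposed group. It neither lists nor bans a head-to-head design.
- *That the crossover rule contradicts an active-comparator group.* Section 3.1 defines crossover for comparator women who were previously unexposed, so the rule does not reach women who enter as recipients of another product.
- *That the study will wrongly report the vaccine as safe.* A null head-to-head result shows no difference between products. The document does not establish that a second maternal product will be in use by the last extraction in 2029.

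What the defence does not remove is the overlap inside Section 3.4, the absence of any statement that the two comparators stay apart, and the mismatch between an active comparator used alone and the primary objective.

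**Conclusion.** The point holds as an inconsistency in the definition of the comparator, worth correcting before the template is reused. Section 3.4 places recipients of another RSV vaccine in both groups and does not prevent pooling, against Section 2, the target trial in 3.1, Table 1, Section 3.9 and the Discussion. The active-comparator option is probably what was meant, but by itself it cannot answer the primary objective or show a risk common to both products.

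The harm is latent. The possible loss, from an RR of 1.5 to 1.43, 1.30 or 1.20 at shares of 10%, 30% or 50%, and to 1.00 with an active comparator only, rests on an assumed share and an assumed common RR. It illustrates direction and scale and is not a forecast.

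**What to change.** - **Section 3.4:** define the comparator for the primary objective as women with no RSV vaccine of any kind in the current pregnancy up to Time zero. Later receipt of any RSV vaccine then falls under the existing censoring rule in Section 3.1.
- **Section 3.4, other products:** state which of the Discussion's two options applies, inclusion in the exposed group or exclusion from the unexposed group, and word the exposed clause to match so that no woman fits both groups.
- **Sections 3.1 and 3.4, and the matching entries in Table 1:** keep the active comparator as a separate, labelled contrast that is not pooled with the unexposed group and is not presented as answering the primary objective.

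The cost is a few wording changes and, if exclusion is chosen, one extra exclusion code. The downside is a slightly smaller comparator pool once other products are in use. The active-comparator option is kept.

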### 3.5. Recommended In- and Exclusion Criteria

Participants are eligible if they:have an identified start of pregnancy date.are enrolled in the healthcare system for a least 12 months prior to Time zero (date of vaccination).have at least one day of follow-up after Time zero for maternal outcomes and at least 10 months of follow-up after the LMP for birth and pregnancy outcomes.

Participants are excluded if they:are exposed to an RSV vaccine prior to the current pregnancy or before or after the gestational week for which the vaccine is licensed (vaccination in a prior pregnancy is permitted).cannot be linked in the data source to their child (mother-child linkage).

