**Pregnancy outcomes**			
Preterm birth [23]	Preterm birth is defined by the WHO as babies born alive before 37 weeks of pregnancy are completed. It is further subcategorised based on gestational age: Extremely preterm (less than 28 weeks) Very preterm (28 to less than 32 weeks) Moderate to late preterm (32 to 37 weeks)	Pregnancies ending with live births	From time of vaccination to before week 37 of gestation (36 weeks and 6/7 days)
Time between vaccination and birth	Time between vaccination and birth in days.	Pregnancies ending with live and non-live births	From time of vaccination to time of birth
Stillbirth [24]	Stillbirth is defined by the WHO as the death of a foetus that has reached a birth weight of 500 g, or if birth weight is unavailable, gestational age of 22 weeks or crown-to-heel length of 25 cm. It is further subcategorised based on gestational age: Late foetal deaths (greater than 1000 g or after 28 weeks) Early foetal deaths (500–1000 g or 22–28 weeks)	Pregnancies ending with live and non-live births	From time of vaccination to end of pregnancy

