**Birth outcomes**			
Low birth weight (LBW) [28]	Low birth weight is defined by the WHO as a weight at birth of less than 2500 g, regardless of gestational age.	Pregnancies ending with live births	From birth until one month after birth
Small for gestational age (SGA) [29]	Small for gestational age is defined by the WHO as a birth weight below the 10th percentile for gestational age and sex. SGA can be caused by placental dysfunction, referred to as foetal growth restriction (FGR), or it can be due to a constitutionally small foetus without any pathological causes. Other possible causes include congenital malformations or infections.	Pregnancies ending with live births	From birth until one month after birth

**Table 3 vaccines-13-00272-t003:** Covariates of interest.

Covariate	Definition
Gestational age at time of vaccination	Gestational age at time of vaccination is defined as the time between the last menstrual period (LMP) and the date of vaccination, measured in weeks.
Calendar time at time of vaccination	Calendar time at the time of vaccination is defined as the specific calendar date of the vaccination, expressed in weeks (e.g., week 48 of the year 2024 or week 12 of the year 2025).
Maternal age	Maternal age at time of vaccination is defined as the age of the pregnant person at the date of vaccination. This age is determined by subtracting the individual’s date of birth from the date of vaccination.

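### Ten months from LMP does not cover gestation plus one month: the full month after birth is guaranteed only for births up to about 39w1d

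*Protocol article*

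**What the plan says.** Three places in the protocol article bear on this point, and a fourth fixes the time origin.

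- **Section 3.4, Study Population.** For data sources that show a pregnancy only after it has ended, the article recommends "a minimum of 10 months of administrative follow-up from the last menstrual period (LMP) in the data source". The reason given is: "This period covers the gestational period plus an additional month to identify offspring outcomes at birth".
- **Section 3.5, eligibility.** The same figure becomes a criterion: "at least 10 months of follow-up after the LMP for birth and pregnancy outcomes". Here it is no longer limited to sources that see only completed pregnancies.
- **Table 2, birth outcomes.** LBW and SGA each have the window "From birth until one month after birth".
- **Table 3, covariates.** Gestational age at vaccination is "defined as the time between the last menstrual period (LMP) and the date of vaccination, measured in weeks", so gestation and the 10-month minimum run from the same date.

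Nothing in the article lengthens the minimum for later births.

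**The concern.** The justification treats gestation as nine months from LMP. A 40-week gestation counted from LMP is 280 days, which is longer than nine months (about 274 days). A woman can therefore satisfy Section 3.5 without her newborn being observable for the whole window that Table 2 sets for LBW and SGA.

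A fixed minimum from LMP also leaves the most time for newborn records after an early birth and the least after a late one. Any incompleteness at the edge of the data would then depend on gestation at birth. Section 3.4 itself warns of selection towards pregnancies that end early, so the threshold should at least have the property claimed for it. Because this is a generic protocol written for others to adapt, the figure and its justification are likely to be copied together.

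**Working it through.** **Inputs**

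- Minimum follow-up: 10 months from LMP (Sections 3.4 and 3.5).
- Window after birth: one month (Table 2, LBW and SGA).
- Origin of gestational age: LMP (Table 3).
- End of the preterm range: 37 completed weeks, 259 days (Table 2).
- Term length: not given in the article, so 40, 41 and 42 weeks are shown as assumptions.
- Average month: 365.25/12 = 30.44 days.

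**The article's figure.** The claim is that 10 months is at least gestation plus one month. Ten months is 10 × 30.44 = 304.4 days, or 43w3d. The latest birth with a full month inside the minimum falls at 304.4 − 30.4 = 273.9 days, or about 39w1d. The claim is reproduced only if gestation is at most nine months from LMP.

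**Days left after birth at the bare minimum** (304.4 − gestation in days), and the minimum that would be needed (gestation + 30.4 days):

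| Birth at | Days from LMP | Days left | Short of 30.4 by | Minimum needed |
|---|---|---|---|---|
| 37w0d | 259 | 45.4 | none | 9.5 months |
| 39w0d | 273 | 31.4 | none | 10.0 months |
| 40w0d | 280 | 24.4 | 6.0 | 310.4 days, 10.2 months |
| 41w0d | 287 | 17.4 | 13.0 | 317.4 days, 10.4 months |
| 42w0d | 294 | 10.4 | 20.0 | 324.4 days, 10.7 months |

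**Does the reading of a month change this?**

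- True calendar months, every LMP date from 2023 to 2026: 10 months is 303 to 306 days, and the limit is 39w0d to 39w5d.
- 30-day months: 300 − 30 = 270 days, 38w4d.
- 31-day months: 310 − 31 = 279 days, 39w6d.
- 28-day months: 280 − 28 = 252 days, 36w0d.
- Ten average months with a 28-day window: 304.4 − 28 = 276.4 days, 39w3d.

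Every count from LMP falls short at 40w0d. Counting the 10 months from conception (14 days later) would move the limit to about 41 weeks, but the article counts from LMP.

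**The case against.** The best defence is that the sentence is a rounded nine plus one months with no demonstrated effect on any estimate. Much of that stands.

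- **It is a minimum.** A longer threshold of 324 days would change eligibility only for LMPs in a band of about 324 − 304 = 20 days before an extraction. Against the five years or more in Section 3.3 (about 1,826 days), that is 20/1,826, about 1% of accrual time, assuming even accrual. Women who leave the source in that interval come on top and cannot be counted from the article.
- **The outcomes occur at delivery.** LBW is "a weight at birth of less than 2500 g, regardless of gestational age", and SGA is likewise judged on birth weight. Delivery falls inside the minimum up to 43w3d. The lost days matter only where weight, diagnosis or linkage is recorded late.
- **Short windows are foreseen.** Section 3.1 ends offspring follow-up at the end of data availability if that comes first.
- **Matching limits differential bias.** Matched women share gestational week and calendar week, so their LMPs and minimum end dates nearly coincide.

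These points limit the size of the problem. They do not make the stated property true, and they do not reconcile Section 3.5 with Table 2.

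A reader might infer three stronger things that the article does not support.

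1. *That preterm births are miscounted.* Preterm birth concerns "babies born alive before 37 weeks of pregnancy are completed", and such births leave more than 45 days inside the minimum. Later births, stillbirths and time to birth are also captured up to 43w3d.
2. *That late births go unlinked, are excluded under Section 3.5, and so inflate the preterm or LBW share.* Section 3.5 lists failure to link as a separate exclusion. Nothing says that linkage takes a month or rests on the 10-month rule, and Section 3.2 leaves lag time and linkage to the assessment of each data source.
3. *That most births lack the month.* Later births do not generally lack it, since 10 months is only a floor. The share born after the limit also needs a gestation distribution that the article does not give. Under assumed Normal distributions with mean 275 to 279 days and SD 11 to 13, it is 52% to 66% beyond 274.4 days. It drops to about 41% beyond 278 days (39w5d) with mean 275 and SD 13.

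**Conclusion.** The point holds as a minor arithmetical error in a stated property of an eligibility threshold. Ten months from LMP guarantees a full month after birth only up to about 39w1d (39w0d to 39w5d by calendar month). At the bare minimum it is short by about 6 days at 40w0d, 13 at 41w0d and 20 at 42w0d.

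The day counts rest only on the article's own LMP origin and the length of a month. The consequence is confined to pregnancies whose data end soon after the minimum, and to LBW or SGA information that reaches the source late. The article gives no figure for that delay, so no bias can be quantified. Strong bias between arms is unlikely given the matching, unless the vaccine changes the length of gestation.

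**What to change.** In Sections 3.4 and 3.5, replace 10 months by about 11 months from LMP, with at least 324 days as the exact figure (42w0d = 294 days, plus 30). Reword the justification to state that assumption. Births after 42w0d would still have less than 30 days at exactly 324 days. A full 11 months (334.8 days) gives an average month for births up to 334.8 − 30.4 = 304.4 days, 43w3d.

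Apply it as an administrative cut: include pregnancies whose LMP lies at least that long before the last data extraction. Keep the cut on LMP and do not replace it by one month after the recorded birth. At a given extraction date, a cut on birth would admit the short pregnancies from the latest LMPs and leave out the long ones, so eligibility would depend on gestation length.

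The cost is a change of figure in two places and a reworded sentence. Pregnancies in the last 20 days or so of LMPs (about 30 with a full 11 months) wait for the next extraction, and at the final extraction they are left out.
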